### Compliance

Compliance will be assessed based on patients' record of compliance as well as serum control at week 3.

### Neuropsychological assessment

The following tests will be used: Brief Assessment of Cognition in Schizophrenia (BACS), Continuous Performance Test-Identical Pairs (CPT-IP), Wechsler Memory Scale^®^-3rd Ed. (WMS^®^-III): Spatial Span, Letter-Number Span, Hopkins Verbal Learning Test-Revised™ (HVLT-R™), Brief Visuospatial Memory Test-Revised (BVMT-R™), Neuropsychological Assessment Battery^® ^(NAB^®^): Mazes, National Adult Reading Test (NART), The Wechsler Abbreviated Scales of Intelligence (WASI), Autobiographical Memory Interview-Short Form (AMI-SF), The Mini-Mental State (MMS).

### Description of measures

*The MINI *[36] covers 18 Axis I disorders and has shown good inter-rater reliability. The MINI has systematic questions covering the various diagnostic criteria of the Axis I disorders. Since many Axis I disorders demand certain obligatory criteria, the MINI has skipping rules if such criteria are not met. Dimensional criteria scores for various disorders, therefore, cannot be established with the MINI. The rating of each criterion on the MINI is absent or present, and the number of positive criteria is summarized as disorder present or absent. The MINI is a relatively brief structured interview, acceptable for the time-frame of the baseline examination.

*The SCID-I *[37] is a semi structured interview for making the major DSM-IV Axis I diagnoses. The SCID is broken down into separate modules corresponding to categories of diagnoses. Most sections begin with an entry question that would allow the interviewer to "skip" the associated questions if not met. For all diagnoses symptoms are coded as present, subthreshold, or absent.

*Affective symptom ratings: The MADRS *[40] is a short and reliable scale devised to be sensitive to change. It is in daily use by both psychiatrists and general practitioners in Norway. The psychometrics (reliability and validity) of MADRS has been shown to be satisfactory. Patients are rated on ten items, each of which has value ranges from 0 (the least pathology) to 6 (the most sever pathology). Sum scores range from 0 to 60, with a scoring of 20 indicating moderate and 30 severe depression [49]. The scale is sensitive to change and covers many, but not all, symptom domains in depression. The MADRS is among the most frequently used depression rating scales in clinical depression trials.

*The IDS *[41] is a well validated 30-item scale translated into many languages. IDS is devised to cover all symptom domains needed for DSM-IV diagnosis. It also comprises symptoms of melancholia and atypical depression and has scaling items allowing for detection of milder levels of symptoms. It has a more balanced weighting of items than the Hamilton Depression Rating Scale and comprises many more symptom domains than the MADRS. IDS is as sensitive as the Hamilton scale and CGI in detecting between group differences.

*The CGI-BP *[42] is a modification of the CGI specifically for use in assessing global illness severity and change in patients with BD. The revised scale and manual provide a focused set of instructions to facilitate the reliability of these ratings of mania, depression, and overall bipolar illness during treatment of an acute episode or in longer-term illness prophylaxis. The modified CGI-BP is anticipated to be more useful than the original CGI in studies of BD. The clinician forms a global judgement both of the severity of the illness as compared to other cases with the same diagnosis and the global degree of change during treatment. Both sub-scales have value ranges from 1 (best) to 7 (worst).

*The PGI-I *requires the patient to rate how much the illness has improved or worsened relative to a baseline state. The illness is compared to change over time and rated as: very much improved, much improved, minimally improved, no change, minimally worse, much worse, or very much worse.

*The SF-36 *[45] is a multi-purpose, short-form health survey with 36 questions. It yields an eight-scale profile of functional health and well-being scores as well as psychometrically-based physical and mental health summary measures, and a preference-based health utility index. It is a generic measure, as opposed to one that targets a specific age, disease, or treatment group. Accordingly, the SF-36 has proven useful in surveys of general and specific populations, comparing the relative burden of diseases, and in differentiating the health benefits produced by a wide range of different treatments.

*The YMRS *[43] is an 11-item scale used to assess the severity of mania. It takes 15-30 minutes to complete. The YMRS has been used in clinical practice since 1978. Ratings are based on self-reporting and clinician observation.

*The MSIF *[46] is a new instrument for rating functional disability in psychiatric outpatients. The MSIF provides discrete ratings of role responsibility, presence and level of support, and performance quality. The MSIF consists of a semistructured interview and detailed rating anchors. The MSIF is an instrument designed to circumvent several limitations with existing functional outcome instruments for longitudinal studies.

*The TEMPS-A *[47] is a self-report questionnaire designed to measure temperamental variations in psychiatric patients and healthy volunteers. Its constituent subscales and items were formulated on the basis of the diagnostic criteria for affective temperaments (cyclothymic, dysthymic, irritable, hyperthymic, and anxious), originally developed by Akiskal [47].

*Everyday memory questionnaire (EMQ) *[50] is a valid and reliable self-report measure of common memory lapses in everyday activities comprising of 27 statements. Examples included "telling someone a story or joke that you have told them once already" and "forgetting where things are normally kept or looking in the wrong place for them". Responses were on a nine-point scale ranging from 'Not at all in the last six months' to 'More than once a day', with high scores indicating more forgetting.

## Adverse events

### Definitions

#### Adverse event (AE)

Any untoward medical occurrence in a patient that may present itself during treatment or administration with a pharmaceutical product, and which may or may not have a causal relationship with the treatment. An AE can therefore be any unfavourable and unintended sign (including an abnormal finding), symptom or disease temporally associated with the use of a medicinal (investigational) product, whether or not related to the medicinal (investigational) product.

#### Serious Adverse Event (SAE)

Any untoward medical occurrence that at any dose:

- results in death,

- is life-threatening,

- requires inpatient hospitalization or prolongation of existing hospitalization,

- results in persistent or significant disability/incapacity or

- is a congenital anomaly/birth defect

#### Unexpected Adverse Event

Any adverse experience associated with the use of the drug/device, the specificity or severity of which is not consistent with the current Summary of Product Characteristics (SPC); or the specificity or severity of which is not consistent with the risk information provided to subjects (in the Informed Consent Document).

#### Attribution to an investigational agent/procedure

Unrelated: The AE is clearly not related to investigational agents.

Unlikely: The AE is doubtfully related to investigational agents.

Possible: The AE may be related to the investigational agents.

Probable: The AE is likely related to the investigational agents.

Definite: The AE is clearly related to the investigational agents.

### Reporting of adverse events

AEs will be reported starting with the first trial related procedure. They will be reported until intake of the last dose of trial medication or last trial-related procedure. When known, the cause of death of a subject in a clinical trial must be reported as a SAE regardless of whether the event is expected or associated with the study medicines or procedures. All SAE occurring during the clinical trial must be reported to the Clinical Study Team Leader [name] or principal investigator [name] by investigational staff within 24 h. Information regarding SAEs must be reported using the SAE form. The report of a SAE may be made by fax or telephone. A telephone report must be followed by a completed SAE Form.

CATEGORY 1: No change required. This category would be for SAEs which in the estimation of the investigators and the RSA that any relationship to the study intervention is questionable and the chances for harm to the future research subjects is unlikely.

CATEGORY 2: Increased monitoring necessary. This category would be for SAEs in which the RSA Committee would require increased frequency or intensity of monitoring.

CATEGORY 3: Intervention or treatment modifications necessary. This category would be for SAEs that would lead to a recommendation to modify the treatment, for example, lowering the dose of the study drug, or extending the treatment interval.

CATEGORY 4: Temporary or permanent suspension of the study. This category would be for SAEs which are judged to be serious enough that no further subjects should be enrolled or treated until a decision about whether the protocol can continue under some modified circumstances. In order to permanently suspend a protocol, a full review of the events by the RSA Committee and the GCRC Advisory Committee will be undertaken.

### Assessment of side effects

The Udvalg for Kliniske Undersøgelser (UKU) Side Effect Rating Scale [51] is used for registration of side effects. UKU is a clinician-rated scale with well-defined and operationalized items to assess the side effects of psychopharmacological medications. The rating is performed by a trained mental health professional on the basis of an interview with the patient and other relevant information from all available sources. In case of discrepancies among the reports, the clinician's observations are given more weight than patient reports. UKU is designed for use in both clinical trials and routine clinical practice. Rating is independent of whether the symptom is regarded as being drug-induced or not. Probability of the causal relationship (or lack of it) of each item to the medication in question is indicated in a separate column, which makes it useful for determining subsequent course of action. Subscales can be useful in assessing differential side effect profiles.

### Emergency procedures

We have procedures for medical emergency:

#### Procedures in case of overdose

For the purpose of this study, all overdoses, with or without associated symptoms, should be reported as AEs. However, all cases of overdose must be reported immediately, within 1 day, if sequela meeting the criteria for a SAE have occurred in association with the overdose. In all instances, the overdose substance must be stated and an assessment whether the overdose was accidental or intentional should be recorded. If the overdose was a suicide attempt, this fact should be clearly stated. AE (serious and non-serious) that occur as a result of an overdose should be recorded on the Case report form (CRF) as "sequelae to overdose" (for example, nausea as sequelae to overdose").

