#### Inclusion and exclusion criteria

The inclusion criteria were designed to ensure that the included patients are typical for patients referred to ECT in Norway in order to have results that are clinically significant, while the exclusion criteria are designed to ensure the patients' safety. Inclusion and exclusion criteria are shown in table 1 and 2.

**Table 1 T1:** Inclusion criteria

Diagnosis of DSM-IV-TR [52] of Bipolar I or Bipolar II disorder as verified by the semi-structured diagnostic interviews SCID [37] or MINI plus [36]. The diagnosis may be supported by information from significant others, and from hospital records. Angst's hypomania checklist [53] is used to increase the detection of hypomanic symptoms. SCID or MINI plus will be used to diagnose the patient.
ECT is indicated.
Severity: meet DSM-IV-TR criteria of depressive episode, MADRS [40] of 25 or above
Treatment resistance: None response to two trials (during lifetime) with mood stabilizers with proven efficacy in bipolar depression (lithium, lamotrigine, quetiapine, olanzapine) and/or antidepressants.
A trial is defined as at least 6 weeks in adequate or tolerated dose as reported by the patient, or patients that have been unable to comply with 6 weeks trials of mood stabilizer or an antidepressant.
None response: Less than 50% reduction in MADRS values or still meet DSM -IV-TR criteria of depressive episode
Inpatients the first week after start of treatment condition
The patients are to be treated by the psychiatrist at the hospital for the whole duration of the study (6 weeks)
Age ≥ 18
Patient competent to give informed consent according to the judgement of the clinician
Written informed consent
Patient sufficiently fluent in Norwegian language to ensure valid responses to psychometric testing (for patients enrolled to neuropsychological assessment: Norwegian as primary language or 12 years attendance of a Norwegian school)

**Table 2 T2:** Exclusion Criteria

Earlier ECT none response
ECT within the last six months
Rapid cycling BD (e.g.4 or more episodes per year)
Use of medication or substances (such as pethidine, alcohol, drugs) incompatible with treatment (medication or ECT). Such medication must be stopped a least 5 half-lives before start of treatment.

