#### Procedures in case of suicide attempt and suicide

Suicide and suicide attempt, irrespective of the method, but in connection with the use of study medicine, should be reported as an AE or a SAE in accordance with the definition provided in section 10. This event should be identified as suicide or suicide attempt, and the method of the suicide or the suicide attempt should be provided.

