## Discussion

This study protocol presents a randomized controlled trial for a population of in-patients with serious, therapy resistant bipolar depressions. We believe that this study is important and needed, and that the main results may influence daily clinical practise. Both bipolar depression and the treatments for bipolar depression are associated with cognitive impairments. This study may give important information of short-and long-time contributions and effects of these different factors.

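### Suicide attempts and intentional overdoses are not serious by rule, so those that meet none of the five listed outcomes escape 24-hour reporting and safety review, and their grade can vary with inpatient status

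*Protocol article*

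**What the plan says.** Five parts of the protocol article bear on this.

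- **Procedures in case of overdose.** The default is that "all overdoses, with or without associated symptoms, should be reported as AEs". Faster reporting depends on outcome: "all cases of overdose must be reported immediately, within 1 day, if sequela meeting the criteria for a SAE have occurred". The substance and whether the overdose was intentional must be recorded, and a suicide attempt must be named as such. Intent does not change the grade or the deadline.
- **Procedures in case of suicide attempt and suicide.** These events "should be reported as an AE or a SAE in accordance with the definition provided in section 10". The event must be identified and its method given. The rule applies "irrespective of the method, but in connection with the use of study medicine".
- **Serious Adverse Event (SAE).** The definition lists five outcomes: death, threat to life, hospitalisation, lasting disability and congenital anomaly. The hospitalisation item reads in full "requires inpatient hospitalization or prolongation of existing hospitalization".
- **Reporting of adverse events.** The 24-hour duty, the SAE form and the four action categories, from no change up to suspension of the study, are all written for SAEs.
- **Table 1, inclusion criteria.** One criterion is "Inpatients the first week after start of treatment condition". The Discussion describes the sample as "a population of in-patients with serious, therapy resistant bipolar depressions".

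**The concern.** Suicidal acts are among the most important safety events in severe bipolar depression, and the article's own Background places the majority of suicides in the depressive phase. One would expect each attempt to reach the people who can change or halt the trial, and to reach them quickly. Under these rules that depends on what the attempt led to rather than on what it was. One of the deciding outcomes, admission to hospital, depends in turn on where the patient was at the time.

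Two things are at stake. Some attempts may never enter expedited reporting or the category review. And the count of serious suicidal events partly reflects ward status as well as behaviour.

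**Working it through.** No arithmetic applies: the point depends on no rate, sample size or effect size. The check is to apply the rules as written to each kind of event.

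| Event | Route to seriousness | Grade | 24-hour report and category review |
|---|---|---|---|
| Completed suicide | Death is a listed outcome; a death must also be reported as an SAE under Reporting of adverse events | SAE | Yes |
| Attempt that is life-threatening or leaves lasting disability, patient in or out of hospital | Listed outcomes, independent of admission status | SAE | Yes |
| Attempt by an inpatient that lengthens the stay | Prolongation part of the hospitalisation item | SAE | Yes |
| Attempt by a discharged patient that leads to admission | Admission part of the hospitalisation item | SAE | Yes |
| Attempt by an inpatient, managed on the ward, with none of the above outcomes | None | AE only | No |
| Attempt by a discharged patient, not admitted, with none of the above outcomes | None | AE only | No |

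Three things follow.

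1. The last two rows are the gap. It exists for inpatients and outpatients alike, because the list has no item for other medically important events and neither special procedure makes the act serious in itself.
2. The fourth and fifth rows can describe the same act. Outside hospital it leads to admission and is an SAE. On the ward it is handled without a longer stay and is an AE.
3. In week 1 every patient is an inpatient under Table 1, so new admission cannot be the trigger. Prolongation, threat to life, death and lasting disability remain open. After week 1 inpatient status depends on discharge, on which the article gives no information. It also states no expected length of stay, so prolongation has no benchmark and is left to the judgement of a treating psychiatrist who knows the allocation.

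As a contrast, Procedures in case of pregnancy has every spontaneous miscarriage handled as an SAE. The article thus already makes one type of event serious by rule, but does not do so for suicide attempts.

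**The case against.** The strongest reply is that grading seriousness by outcome is coherent, that the article applies it consistently, and that no suicidal act is lost. Every overdose is at least an AE with intent recorded. Every attempt must be identified with its method. The Statistical analysis section plans an analysis of treatment-emergent adverse events, which would include attempts graded non-serious. Table 2 excludes patients judged at high suicidal risk, and the Withdrawal criteria remove patients who come to meet an exclusion criterion, with the reason noted and a final evaluation. All of this stands. It limits the gap to speed, review and grading; it does not close it, because none of these provisions triggers a 24-hour report or a category decision.

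A second reply is that the article condenses a longer document. The reference to a section 10 that the article does not contain suggests carried-over text, and the full protocol may hold a further criterion. That cannot be excluded. But the point does not rest on missing detail: the reporting rules are stated in the article, and together they give this result.

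Three stronger readings may tempt a reader, and the documents support none of them.

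- *That a completed suicide could be filed as a non-serious AE.* The loose wording covers suicides and attempts together, but it defers to the definition, where death is listed, and deaths are separately reportable as SAEs.
- *That the hospitalisation item is closed to inpatients.* Only its admission part is. The prolongation part exists for patients already admitted, and an attempt on an acute ward may well lengthen a stay; the article does not say either way.
- *That SAE counts will be biased between arms.* This would need discharge patterns and attempt rates by arm, and the article gives neither. The inpatient requirement for week 1 is the same in both arms. Any numerical example would only restate its own assumptions.

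**Conclusion.** The point holds in limited form. Suicide attempts and intentional overdoses are not serious by default. Those that are not life-threatening, leave no lasting disability and neither cause admission nor prolong a stay are recorded as AEs, but fall outside the 24-hour report and the four-category review. The same act may be graded differently for an inpatient and for a discharged patient.

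The size cannot be given: the documents do not show how often such events would occur, how many patients remain in hospital after week 1, or any difference by arm. The conclusion assumes only that the reporting rules are applied as printed and that the full protocol adds no overriding rule. It does not touch the primary efficacy analysis. It is a weakness in safety oversight that is worth correcting because the events matter and the correction is small.

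A related wording problem adds to it. The suicide procedure is tied to the use of study medicine and does not name electroconvulsive therapy (ECT), so its application to the ECT arm is unclear.

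**What to change.** Add one sentence to each of the two procedures, on overdose and on suicide attempt and suicide. Each should state that every intentional overdose, or every suicide attempt, in either arm, is reported on the SAE form within 24 hours and enters the review under Reporting of adverse events, regardless of sequelae or inpatient status. While editing, replace the reference to section 10 with one to the article's own SAE definition. This uses the same device that the article already applies to spontaneous miscarriage.

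The cost is two sentences and a few more SAE forms. No other reporting rule needs to change.

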#### Procedures in case of suicide attempt and suicide

Suicide and suicide attempt, irrespective of the method, but in connection with the use of study medicine, should be reported as an AE or a SAE in accordance with the definition provided in section 10. This event should be identified as suicide or suicide attempt, and the method of the suicide or the suicide attempt should be provided.

#### Procedures in case of pregnancy

Pregnancy itself is not regarded as an AE unless there is a suspicion that the study medicine may have interfered with the effectiveness of a contraceptive medication. However, the outcome of all pregnancies (spontaneous miscarriage, elective termination, normal birth or congenital abnormality) must be followed up and documented even if the patient was discontinued from the study.

All reports of congenital abnormalities/birth defects are SAEs. Spontaneous miscarriages should also be reported and handles as SAEs. Elective abortions without complications should not be handled as AEs. All outcomes of pregnancy must be reported to the principal investigator.

Female patients of childbearing potential must be using a reliable method of contraception. Reliable methods of contraception include hormonal contraceptives (e.g. oral contraceptives or long term injectable or implantable hormonal contraceptive), double-barrier methods (e.g. condom and diaphragm, condom and foam, condom and sponge), intrauterine devices and tubal ligation. Female patients must have a negative urine human chorionic gonadotropin (HCG) test at enrolment.

